**Fig. 2 Fig2:**
[figure not shown]
The modules of VR-SOAP

All participants will end with the Communication and Interaction skills module (4 sessions), in which experiences, knowledge and skills from the other modules are integrated and applied.Module 5: Domain—Communication and Interaction skills; Treatment components—practicing conversations, job interviews, attending a party—with a focus on social skills, e.g. responding and sending, affiliative, instrumental role and interactional skills.

##### Session 3–14

At least half of every session is spent in VR. Exercises and role-plays are guided by the therapist and evaluated afterwards, using cognitive-behavioural techniques. They can be adapted and repeated during the session. At the end of each session, homework is given, aimed at applying the session’s insights and obtained skills in daily life, with exercises designed for achieving the patient’s social goals. These exercises will be followed up at the beginning of the next session.

VR-SOAP consists of animated, interactive virtual social environments, programmed by CleVR B.V. in Unity3D software. The virtual social environments that are used for social interactions include the following: a café, shopping street, office, living room, supermarket, park and bus. Characteristics of social situations can be customized, such as the number, gender and ethnic appearance of the virtual characters (avatars) present in the social situation. Additionally, the behaviour of avatars (gestures, facial emotion expression and speech) can be controlled in real time. Participants wear an Oculus Rift head-mounted display with an HD resolution of 2160 × 1200 and a field of view of 110°, and navigate through the virtual environments using a controller. Therapists speak with the patient (via a microphone with voice distortion) as an avatar and can control the movement and gestures of avatars.

#### VRelax (active control condition)

The control condition also consists of 14 individual weekly VR sessions (60 min) with a therapist, but aims at relaxation, using the VRelax app, programmed by VRelax B.V [36]. Participants wear the Oculus Quest 2 head-mounted display and watch 360° videos with interactive game elements. Multiple natural environments are available, e.g. swimming with dolphins, a beach and a forest. Audio clips of guided relaxation exercises such as progressive muscle relaxation and meditation are embedded in the videos. Participants can navigate between environments, activate relaxation exercises and use game elements by looking at hotspots within the videos. Similar to VR-SOAP, the sessions are provided using a detailed treatment protocol and both therapists and participants use a workbook. The VRelax therapy is carried out by therapists with at least a bachelor’s degree in psychology or professionals with clinical experience with the patient population.

In session 1, the participant and therapist identify the main sources of stress for the participant. All remaining VRelax sessions consist of practicing stress management techniques (e.g. grounding or body scanning), psychoeducation (e.g. the effect of stress on mental health) and VR relaxation. Half of each session is allocated to relaxation in VR.

VRelax is selected as the active control condition to control for non-specific treatment effects of VR interventions. VRelax does not target underlying causes of impaired social functioning. In line with this, it has been shown that VRelax does not have an effect on social functioning [37].

### Measures

Table 1 provides an overview of the measures used in this study.

**Table 1 Tab1:** Measures used in this study

Domain	Instrument	Method	Baseline assessment (T0)	Post-treatment assessment (T1)	Follow-up assessment (T2)
**Primary outcome measures**					
Social Functioning in daily life	Diary protocol mapping social interactions, activities and momentary mental states	Experience Sampling Method (ESM)	x	x	x
**Secondary outcome measures**					
Social functioning	Social Functioning Scale (SFS)	Questionnaire	x	x	x
Interpersonal behaviour	Inventory Interpersonal Situations (SIG)	Questionnaire	x	x	x
Self-esteem	Self-Esteem Rating Scale Short-Form (SERS-SF)	Questionnaire	x	x	x
Social Interaction Anxiety	Social Interaction Anxiety Scale (SIAS)	Questionnaire	x	x	x
Stigma	Internalized Stigma of Mental Illness Scale (ISMI)	Questionnaire	x	x	x
Dating and assertion	Dating and Assertion Questionnaire (DAQ)	Questionnaire	x	x	x
Paranoid Thoughts	Revised Green et al. Persecutory and Paranoid Thought Scale (R- GPTS)	Questionnaire	x	x	x
Theory of Mind	Hinting task	Task	x	x	x
Emotion Recognition	Bell-Lysaker Emotion Recognition Task (BLERT)	Task	x	x	x
Negative Symptoms	Brief Negative Symptom Scale (BNSS)	Semi-structured Interview	x	x	x
Psychotic symptoms	Positive and Negative Syndrome Scale (PANSS)	Semi-structured Interview	x	x	x
**Other measures**					
Presence	I-group Presence Questionnaire (IPQ)	Questionnaire		x	
Demographic and clinical background	Questions	Questionnaire	x	x	x
Diagnostic	Mini-SCAN	Semi-structured Interview	x		
Therapeutic Alliance	Session Rating Form	Questionnaire	S1- S14		

#### Primary outcome

##### Quantity and quality of social contacts, leisure activities and social participation

Three domains of social functioning are measured with the experience sampling method (ESM). Participants will complete ESM diaries at semi-random moments, prompted by a signal on their phone, five times a day for 2 weeks. Items are scored on a Likert scale ranging from 0 (not at all) to 7 (very) or as multiple-choice questions.

The diary consists of 35 items and will take 2–3 min to complete. Each time the participant is asked whether he or she is or has engaged in any (social) activity, at that particular moment, and since the previous questionnaire. If the participant is engaged in a (social) activity, the participant is asked additional questions, e.g. I feel accepted by this company. The diary parallels the five modules such that different underlying processes targeted in VR-SOAP are assessed (e.g. we expect the item: “I find this activity pleasurable”, to be associated with negative symptoms.).

#### Secondary outcomes

##### Social functioning

Social functioning will be assessed using the Social Functioning Scale (SFS). The SFS is developed for patients with schizophrenia and measures specifically those areas crucial for community functioning [38]. Additionally, the SFS distinguishes between a lack of competence and a lack of performance [38]. The SFS consists of 78 questions with varying response formats. The total score of the SFS is the mean of the seven subdomains; social engagement/withdrawal; interpersonal behaviour; pro-social activities; recreation; independence-competence; independence-performance; employment/occupation [39]. The SFS is self-administered separately by the patient and a relative or friend. The results of both will be reported.

##### Determinants of impaired social functioning

The identified determinants of impaired social functioning and subsequent domains addressed in the five modules of the VR-SOAP interventions were admitted as secondary outcomes.*Negative symptoms*: The Brief Negative Symptom Scale examines blunted affect, alogia, asociality, anhedonia and avolition [40]. The BNSS consists of 13 items rated from normal to very severe (6-point) and is administered as a semi-structured interview. Item scores are based on the week before the interview.*Social cognition*: Social cognition will be assessed by means of two tasks. The Hinting Task assesses the capacity to infer the true meaning behind indirect speech [41]. The Hinting Task depicts ten short social situations in which a hint is dropped. Each narrative and question is read aloud by the test leader. The Dutch version of the Bell and Lysaker emotion recognition task (BLERT) consists of 35 videos in which actors narrate a situation and express an emotion or remain neutral [42]. Emotions that can be expressed are as follows: happiness, sadness, fear, anger, disgust and surprise. After each video, the patient is asked to choose the correct emotion out of the seven options.*Paranoid ideation*: The Revised Green Persecutory Thoughts Scale is a self-report questionnaire consisting of 8 items measuring ideas of reference and 10 items measuring ideas of prosecution [43]. Both subscales will be analysed separately.*Social anxiety*: The Social Interaction Anxiety Scale (SIAS) is a self-report questionnaire of 19 items measuring fear of social interaction [44]*Self-esteem*: The Self-esteem Rating Scale Short-form is a twenty-item self-report questionnaire measuring positive and negative self-esteem separately [43, 45]*Self-stigma*: The Internalized Stigma of Mental Illness scale assesses stigma with 29 items on five different subscales; Alienation, Stereotype Endorsement, Discrimination Experience, Social Withdrawal, Stigma Resistance [46].*Social behaviour*: Social behaviour (e.g. social interaction and assertiveness) will be measured by means of two assessment instruments. The Inventory of Interpersonal situations (ISS) measures an interactive concept of social anxiety and avoidance using 50 items describing hypothetical responses to social situations that the patient will score on two dimensions; frequency and discomfort [47]. The Dating and Assertion Questionnaire is a self-report questionnaire that consists of 18 items to identify appropriate dating and assertiveness behaviours [41, 48]. The first 9 items inquire the likelihood of engaging in dating and assertiveness behaviours, whereas the latter 9 items probe the degree of discomfort in doing so or incompetence otherwise [41].

##### Other

Psychotic symptoms will be assessed by means of the Positive and Negative Syndrome Scale (PANSS). The PANSS is a semi-structured interview that assesses positive symptoms, negative symptoms and general psychopathology [49]. The PANSS consists of 30 items pertaining to the week prior to the interview and is scored from normal to very severe (7-point).To measure presence, defined as “the sense of being in the virtual environment” [50] the I-group Presence Questionnaire [51] is administered once at post-treatment. The IPQ is a self-report questionnaire of 14 items.

##### During sessions

To measure therapeutic alliance, the patient fills in the Session Rating Form (SRS) in the therapist workbook at the end of each session.

### Study Procedures

#### Recruitment

Patients who might be eligible for participation will be contacted by their treating clinician (psychiatrist, doctor, psychologist, nursing specialist). The treating clinician informs the patient about the study. If the patient is interested and agrees to share contact details, the patient will be screened and informed by the researchers, both written and verbal. Additionally, the clinician will be contacted by the researcher to determine whether impairments are present in the following domains: work and education, (social) leisure activities or social contacts. Subsequently, the patient will receive written information and is given 1 week to consider participation. If the patient agrees to participate, the informed consent will be signed by the participant and the research assistant. The baseline assessment (T0) will be conducted afterwards. After randomization, a summary of the baseline assessment is provided to the patient and the therapist to guide the selection of VR-SOAP modules.

#### Assessment

Trained independent research assistants blinded to treatment allocation will do the post-treatment and follow-up assessments. Blinding is achieved by instructing therapists and participants to not communicate group allocation to assessors. To evaluate blindness, the assessor fills in the self-report form. A sensitivity analysis of data acquired by blinded assessors only will be done to investigate the effect of blinding.

Participants who are completing the ESM will be contacted at least twice during the data collection period to ensure a high response rate, with additional follow-ups if the response rate falls below 33%.

#### Randomization

With the open-source “Research Randomizer” (randomizer.org), a list is created for each participating centre in which each participant number is assigned either to VR-SOAP (experimental condition) or VRelax (active control condition). Randomization is 1:1, there are no randomization blocks. To guarantee concealment of treatment allocation, the bureau of randomization assigns each participant after baseline assessment to a participant number in order of inclusion and communicates the allocation to the researcher.

Baseline assessments are repeated in the week after the last treatment (T1) and 6 months after the end of treatment (T2).

#### Protocol fidelity

Therapists complete a training, which amounts to 3 days for VR-SOAP therapists and 1 day for VRelax therapists. This difference is due to the extensive CBT and modular structure of VR-SOAP. Additionally, therapists will attend monthly supervision in which all ongoing cases will be discussed to ensure the quality and fidelity of both treatment conditions. Supervision will be provided by a trained (VR) therapist who is part of the research group. Every therapist fills in a session form after each session to register protocol fidelity and anomalies.

Deviations in the research protocol will be communicated to METc, the sponsor and participating centres and registered in the Dutch Trial Register.

### Statistical analyses

All analyses will be intention to treat. The intention-to-treat analysis will include all participants who have given their informed consent and have been randomized to a group after the baseline assessment. Descriptive statistics will be calculated for all clinical and outcome variables as well as for sociodemographic variables. Means that differ significantly at baseline between groups will be added as a covariate to the analysis. For each domain of the primary outcome variable, mean total scores are calculated based on all 70 scores (5 times a day × 14 days = 70 scores). Multilevel mixed-model regression analysis will be used for the analysis of the primary outcome (ESM). Repeated assessments will be nested within participants and all models will include a random intercept for participant. The method of estimation is maximum likelihood and the covariance structure independent. Treatment effects are evaluated with group (VR-SOAP or VRelax) × time (baseline, end of treatment, follow-up) interaction terms. Measures taken after treatment and follow-up will be evaluated separately.

A mediator analysis will be conducted to identify the underlying processes of change in the primary outcome. The primary analysis will be followed up with sensitivity analysis on completers, i.e. patients who completed 12 or more sessions. In case of missing data, participants will be included in the analysis with the exclusion of the missing datapoint. If the overall proportion of missing questionnaire items was less than 5% and the participant had less than one missing item for every ten items, their mean at that specific time point was used to impute the missing data.

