**Fig. 1 Fig1:**
[figure not shown]
Flowchart of study

Both groups continue to receive treatment as usual (TAU) during the study, which can include antipsychotic medication and contacts with a psychiatric nurse and/or psychiatrist. Both groups participate in an assessment before the start of treatment (T0), at post-treatment (T1) and 6 months after the end of treatment (T2).

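### If the three wave means enter one joint model, the stated random-intercept, independent structure forces equal correlation between unequally spaced waves, which can make the 6-month follow-up test liberal and the post-treatment test conservative

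*Protocol article*

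**What the plan says.** All of this is in the protocol article, Statistical analyses, unless another section is named.

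- **Outcome.** "For each domain of the primary outcome variable, mean total scores are calculated based on all 70 scores". This points to one value per domain, participant and wave.
- **Random effects.** "Repeated assessments will be nested within participants and all models will include a random intercept for participant".
- **Estimation and covariance.** "The method of estimation is maximum likelihood and the covariance structure independent".
- **Treatment effect.** "Treatment effects are evaluated with group (VR-SOAP or VRelax) × time (baseline, end of treatment, follow-up) interaction terms".
- **Two time points.** "Measures taken after treatment and follow-up will be evaluated separately". The text does not say whether this means two contrasts from one model or two models.
- **Timing.** There are 14 weekly sessions (VR-SOAP section). T1 is in the week after the last session and T2 is 6 months after the end of treatment (Design and Randomization sections). T1 is therefore roughly 3 months, and T2 roughly 9 months, after baseline.

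The section names no random slope, participant-by-wave effect, unstructured alternative or robust standard error.

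**The concern.** A participant random intercept with independent residuals implies compound symmetry: equal variance at every wave and the same correlation between every pair of waves. With unequal spacing, one would usually expect baseline to correlate less with T2 than with T1. The model nevertheless estimates one pooled within-person variance and uses it for both the T0-to-T1 and the T0-to-T2 contrast, which may need different ones.

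The Discussion section states the hypothesis at both post-treatment and follow-up, so both contrasts matter. A standard error that is too small at T2 raises the chance of a false claim of lasting benefit. One that is too large at T1 costs power. This is not a detail left to a later analysis plan, because the article itself fixes the structure.

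**Working it through.** **The plan's own figure.** The article gives no figure that depends on the wave covariance. Its sample size does not, but it supplies the N used below. With a difference of 0.5, SD 0.9, two-sided alpha 0.05 and power 0.80, n per arm = 2 × (1.960 + 0.842)² × 0.81/0.25 = 50.9, so 51 per arm and 102 in total, as stated. Then 102 × 1.13 = 115.3, rounded up to the stated 116.

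**Inputs not in the article.** The between-wave correlations and variance shares are assumptions, shown as ranges.

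**Step 1: wave means, one joint three-wave model.** Take complete data and equal variances, and let ρ01, ρ02 and ρ12 be the correlations T0–T1, T0–T2 and T1–T2, with mean ρ̄. The model's within-person variance estimates σ²(1 − ρ̄), while the contrast from T0 to wave k needs σ²(1 − ρ0k). Hence:

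- model SE / true SE = √[(1 − ρ̄)/(1 − ρ0k)]
- type I error = 2 × [1 − Φ(1.96 × ratio)]

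For 0.6/0.4/0.6 (in the order ρ01/ρ02/ρ12), ρ̄ = 0.533:

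- T1: √(0.467/0.4) = 1.08, type I error 3.4%
- T2: √(0.467/0.6) = 0.88, type I error 8.4%

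| ρ01/ρ02/ρ12 | T1 ratio | T1 type I | T2 ratio | T2 type I |
|---|---|---|---|---|
| 0.6/0.6/0.6 | 1.00 | 5.0% | 1.00 | 5.0% |
| 0.6/0.4/0.6 | 1.08 | 3.4% | 0.88 | 8.4% |
| 0.7/0.5/0.7 | 1.11 | 3.0% | 0.86 | 9.3% |
| 0.7/0.5/0.6 | 1.15 | 2.4% | 0.89 | 8.0% |
| 0.8/0.5/0.6 | 1.35 | 0.8% | 0.86 | 9.3% |

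T2 is liberal whenever ρ02 is below the mean of the three. T1 is conservative whenever ρ01 is above it.

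**Step 2: simulation check.** Maximum-likelihood random-intercept fits with N = 102 and correlations 0.7/0.5/0.6 (600 runs) gave:

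- T1: model SE 0.175 against empirical 0.155, type I error 3.2%
- T2: model SE 0.175 against empirical 0.197, type I error 7.5%

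This agrees with the formula in direction and approximate size.

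**Step 3: separate two-wave models on wave means.** With two waves there is only one correlation, so no equality constraint binds. Simulation with the same correlations (300 runs each) gave SE ratios of 0.985 for T0–T1 and 0.989 for T0–T2, with type I error of 4.7% and 3.3%. Maximum likelihood alone would give about √(100/102) = 0.990. There is no material error.

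**Step 4: momentary records, if those are the rows.** Let the participant share of the variance be 0.30 and the participant-by-wave share w, so that e = 0.70 − w, with m records per wave. The true contrast variance is proportional to w + e/m. The model uses r/m, where r = e + (2/3)w × 3m/(3m − 1). For w = 0.05 and m = 50:

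- true: 0.05 + 0.65/50 = 0.0630
- model: 0.6836/50 = 0.01367
- SE ratio: √(0.01367/0.0630) = 0.47, type I error 36%

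Simulation of this case (120 runs) gave 39% at T1 and 33% at T2. At the mild end, w = 0.01 with m = 23 gives a ratio of 0.87 and 8.8%. With w = 0.10 and m = 70 it gives 0.30 and 56%. The value 23 is 33% of 70. In the Assessment section, 33% is only the response rate that triggers extra contact, and it serves here as an illustrative low count. The formula is the same for T1 and T2.

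**The case against.** The strongest reply is that the text may already avoid the problem. The sentence on separate evaluation can mean one T0–T1 model and one T0–T2 model, and on wave means step 3 shows that this removes the error. That stands. However, the time factor is written with three levels, which makes two contrasts from one joint model at least as natural a reading, and the text does not settle it.

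A second reply is that equal correlations give correct standard errors, and the article reports no correlations. That also stands, so the error is conditional.

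A third is that the word independent may describe the covariance of the random effects. With a single random intercept it would then have no content, and default independent residuals would still give compound symmetry. This reply does not rescue the model. It does mean that deleting the word would change nothing and that the structure has to be replaced.

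A reader might go further and infer that the model simply leaves out participant-by-wave variation, with false-positive rates of 20% or more and the worst damage at follow-up. The article does not support that:

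- The sentence on mean scores, and the use of assessment for T0, T1 and T2, favour one mean per wave as the unit. On wave means the residual *is* the participant-by-wave variation, so nothing is omitted.
- The large rates belong only to a model of momentary records, which the term multilevel does not rule out but which the text does not clearly describe.
- Under that model T1 and T2 are affected alike. On wave means, the T1 standard error can be further from correct than the T2 one (1.35 against 0.86), though in the conservative direction.

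**Conclusion.** The point holds conditionally. As written, a joint three-wave model of wave means is compound symmetric. If the T0–T2 correlation is lower than the other two, type I error at T2 is about 8% to 9% at a nominal 5%. In the same scenarios T1 runs at about 1% to 3.4%, which is lost power. These sizes rest on assumed correlations, equal variances and complete data.

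It would be wrong to conclude that the planned standard errors are wrong as such. They are right under equal correlations, and materially right under separate two-wave models of wave means. The much larger inflation, from about 9% to over 50% under assumed variance shares, applies only if momentary records enter the model with the stated random intercept alone. The sample size is unaffected. This is a moderate weakness in the primary analysis that is cheap to remove.

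**What to change.** 1. State that the rows of the primary model are wave means, one per participant and wave for each domain, and what separate evaluation of T1 and T2 means.
2. Replace the random intercept and independent structure with an unstructured 3 × 3 within-participant covariance, preferably fitted by REML, and take the T1 and T2 group-by-time contrasts from that one model. With complete data each contrast then has the standard error of a comparison of change scores between arms, so its error rate does not depend on the correlation pattern. This follows from the model and was not simulated.
3. If momentary records are to be modelled instead, add a participant-by-wave random intercept to the participant one.

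The cost is a sentence or two in the plan and a small change in code. An unstructured 3 × 3 matrix has six parameters against two for compound symmetry, so four more per domain, which is little with 116 participants.

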#### Sample size calculation

Mean effect sizes of current interventions on social functioning are around *d* = 0.5 [52]. With the G-power software package, the effect size is calculated based on an estimated effect size on the primary outcome of 0.5 [13, 53, 54], two groups, statistical power of 0.8, alpha of 0.05 and a standard deviation of 0.9. The required sample size of 102, with a correction for an estimated 13% [55] drop-out, amounts to *N* = 116.

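### The primary test is, on its ordinary reading, a change-from-baseline contrast: valid, but less precise than one using the pre-randomization ESM score, by (1 − ρ)/2 of its variance

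*Protocol article*

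**What the plan says.** Under Statistical analyses, the protocol article defines the outcome unit: "For each domain of the primary outcome variable, mean total scores are calculated based on all 70 scores". Each participant therefore contributes one mean per domain at T0, T1 and T2. On the model it says "Repeated assessments will be nested within participants and all models will include a random intercept for participant" and "The method of estimation is maximum likelihood and the covariance structure independent". The treatment effect is defined by "Treatment effects are evaluated with group (VR-SOAP or VRelax) × time (baseline, end of treatment, follow-up) interaction terms", and "Measures taken after treatment and follow-up will be evaluated separately". Baseline is thus one level of the outcome's time factor.

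The only rule for baseline adjustment is "Means that differ significantly at baseline between groups will be added as a covariate to the analysis". The text does not say whether the model keeps a group main effect, and it gives no correlation between baseline and later ESM scores.

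Under Randomization, "the bureau of randomization assigns each participant after baseline assessment", so the T0 assessment precedes allocation. Under Sample size calculation, the trial is sized as a comparison of "two groups, statistical power of 0.8, alpha of 0.05", with an effect of 0.5 and an SD of 0.9. This gives 102 evaluable participants and 116 after a drop-out correction. No baseline correlation enters that calculation.

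**The concern.** With group, time and their interaction in the model, the group-by-time term at T1 (or T2) is the difference between arms in mean change from T0. The model then estimates a baseline group difference that randomization makes zero in expectation, and subtracts that estimate with full weight. When baseline predicts the later score only moderately, the subtraction adds more noise than it removes.

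What is at stake is precision. The sample size has no slack, and the baseline ESM score, which could sharpen the primary comparison, is collected anyway. The rule that admits a baseline covariate only after a significant difference leaves most chance imbalances unadjusted. If it were triggered by baseline ESM itself, the same measurement would be both an outcome level and a covariate in one model.

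**Working it through.** **The plan's own figure.** Inputs from Sample size calculation: effect 0.5, SD 0.9, power 0.80, alpha 0.05. Sidedness is not stated.
- Raw difference 0.5 with SD 0.9, two-sided normal formula: n per arm = 2 × (1.960 + 0.842)² × 0.81 / 0.25 = 50.9, so 51 per arm and 102 in total. The stated 102 is reproduced.
- Standardized d = 0.5, two-sided: 2 × (1.960 + 0.842)² / 0.25 = 62.8, so 63 per arm and 126 in total. This does not give 102.
- Standardized d = 0.5 with a one-sided t-test also gives 51 per arm.

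The section names the effect as d and also gives an SD, so power is shown below on both readings of 0.5.

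**Variances.** A participant intercept with independent residuals implies equal variances and one common correlation ρ. In units of the variance of a plain two-group difference at one time point, with complete data:
- planned contrast (difference in change): 2(1 − ρ)
- baseline as covariate, or one common T0 mean: 1 − ρ²
- ratio, adjusted to planned: (1 + ρ)/2, so the reduction is (1 − ρ)/2

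The reduction is positive for every ρ below 1. The planned variance exceeds 1, the plain two-group value, whenever ρ < 0.5.

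**Check of the algebra.** Generalized least squares for the three-time model with 51 per arm gave T1 variances, free against common baseline, of 0.0471 and 0.0329 at ρ = 0.4 (30% lower) and 0.0235 and 0.0200 at ρ = 0.7 (15% lower). A simulation at N = 102 with 4,000 replicates gave reductions of 29.2% and 12.7%. Both estimators averaged about 0.50, the true value.

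**Size over assumed ρ.** Power is from the noncentral t, two-sided 0.05, 51 per arm, with the effect divided by the square root of the relative variance:

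| ρ (assumed) | Planned variance | Adjusted variance | Reduction | Power if d = 0.5: planned / adjusted | Power if 0.5 is raw, SD 0.9: planned / adjusted |
|---|---|---|---|---|---|
| 0.2 | 1.60 | 0.96 | 40% | 0.51 / 0.72 | 0.59 / 0.81 |
| 0.4 | 1.20 | 0.84 | 30% | 0.63 / 0.78 | 0.72 / 0.86 |
| 0.5 | 1.00 | 0.75 | 25% | 0.71 / 0.82 | 0.79 / 0.89 |
| 0.7 | 0.60 | 0.51 | 15% | 0.90 / 0.94 | 0.95 / 0.97 |
| 0.8 | 0.40 | 0.36 | 10% | 0.98 / 0.99 | 0.99 / >0.99 |
| 0.9 | 0.20 | 0.19 | 5% | >0.99 / >0.99 | >0.99 / >0.99 |

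**The case against.** The strongest reply is that nothing here is an error. A group-by-time interaction with a random intercept is a conventional longitudinal analysis, and its test is valid under randomization. This stands, so the point concerns efficiency.

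Second, the free baseline is inferred. The article names interaction terms and a random intercept but not a group main effect. If that effect is omitted, both arms already share a T0 mean and nothing is gained. This also stands, although keeping the main effect is the ordinary reading. One sentence in the plan would settle it.

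Third, ρ may be high. The outcome averages up to 70 prompts, and at ρ = 0.8 or more the power gain is negligible. The documents neither support nor exclude this.

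Fourth, the significance-triggered rule might bring baseline ESM in when the arms differ. It might, but it makes adjustment depend on a chance test result and does nothing when the test is not significant.

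A reader might infer two stronger claims:
- **That the planned estimate is biased by regression to the mean.** Given an observed baseline difference D, the change contrast is shifted by −(1 − ρ)D. Over randomizations D averages zero, so there is no bias.
- **That the trial is already short of its stated power.** This depends on reading 0.5 as a standardized, two-sided effect (power 0.71 for a plain comparison of 51 per arm). Read as a raw difference with SD 0.9, the inputs reproduce 102.

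**Conclusion.** The point holds as a matter of efficiency. On the ordinary reading, the planned contrast is valid and unbiased, and its variance can be reduced by (1 − ρ)/2 using a measurement taken before randomization. A single range such as 15% to 30% would presuppose ρ between 0.4 and 0.7, which the protocol does not give. Over assumed ρ from 0.2 to 0.9 the reduction runs from 40% to 5%. Below ρ = 0.5 the planned contrast is noisier than the plain two-group comparison used for sizing.

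The result assumes a retained group main effect, complete data, and the equal variances and common correlation that the stated model implies. It is a worthwhile improvement to make before analysis and does not threaten the validity of the trial.

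**What to change.** For the primary ESM outcome, pre-specify one of the following in place of the significance-triggered rule for baseline ESM:
1. **Preferred:** a constrained longitudinal model with T0, T1 and T2 as outcomes, one common T0 mean for both arms, and separate group effects at T1 and T2. It keeps participants whose T0 ESM score is missing.
2. **Alternative:** T1 and T2 as outcomes, with group, time, group × time, baseline score and baseline × time as fixed terms. This costs about one or two degrees of freedom and loses anyone without a usable T0 ESM score.

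In either case, state whether a group main effect is included, and report the adjusted group difference at T1 and at T2 with confidence intervals. No new data or visits are needed, because T0 ESM is already scheduled before randomization. The cost is a change of analysis wording.
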